**Fig. 8 Fig8:**
[figure not shown]
Time frame for data collection

**Fig. 9 Fig9:**
[figure not shown]
SPIRIT schedule of enrollment, interventions, and assessments. Adapted from SPIRIT 2025 guidelines [25]. Notes: X = assessment occurs at this timepoint; — = intervention delivery/exposure period. EOT = end of antibiotic treatment (typically day 3–7 depending on course). Follow-up windows: 1 month (± 7 days), 3 months (± 14 days), 6 months (± 21 days). NA not applicable (no biological specimens collected; harms not systematically assessed due to minimal-risk behavioral intervention)

### Statistical analysis plan

#### Primary outcome analysis

The primary outcome will be analyzed as a categorical variable (adhered vs. not adhered). The chi-square test or Fisher’s exact test (if expected counts are < 5) will be used for between-group differences. A mixed-effects logistic regression model will estimate the odds ratio (OR) for adherence in the intervention vs. control group, adjusted for baseline characteristics (e.g., age, sex, MPI category, education). Hospital will be included as a random intercept to account for clustering due to stratified block randomization by site.

Based on the multidimensional poverty index [5], which categorizes poverty into four subgroups, namely (1) not deprived, (2) vulnerable to deprivation, (3) deprived, and (4) severely deprived, a subgroup analysis will be carried out to assess the effect of intervention across these subgroups. Results will be reported as adjusted odds ratios (aORs) with 95% confidence intervals (CIs) and *p* values.

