### Patients’ population and sample size

Participants will include adults (≥ 18 years) with physician-diagnosed uncomplicated UTI who meet all inclusion criteria: (1) confirmed UTI diagnosis, (2) prescribed oral antibiotics (tablet or capsule), (3) having obtained their prescribed medication, (4) willing to participate, and (5) able to provide informed consent.

Patients with polypharmacy (taking five or more medications) [26] are excluded to minimize the risk of confounding factors related to multiple treatment regimens and potential medication interactions that could affect adherence. Patients with complicated UTI (pyelonephritis, sepsis, structural abnormalities) and with multiple comorbidities will be excluded. In addition, patients with cognitive impairment and pregnant or breastfeeding women will also be excluded from the study. Participants may discontinue participation at any time upon request or if they experience clinical deterioration or become ineligible (hospitalization or transfer). All discontinuations and reasons will be documented and summarized in the CONSORT flow diagram.

Eligible uncomplicated UTI patients will be approached during their outpatient visits in the urology department, and written informed consent will be obtained before participation. The patients will be recruited in the current study using the SEAR (Screened, Eligible, Approached, Randomized) framework [27].

The sample size was calculated using R statistical software (version 4.3.0) with “pwr” package (version 1.3.0). Based on our pilot study findings, which demonstrated a 16% improvement in adherence (64.3% in the intervention group vs. 48.3% in the control group), we used this observed effect size (Cohen’s *h* = 0.32) for power calculation. To detect this clinically significant difference in adherence rates with 80% power at a 5% significance level (two-sided test), 152 participants per group (304 total) would be required. Accounting for an estimated 15% attrition rate, informed by our pilot study, we will enroll 179 participants per group (358 total).

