##### Knowledge and attitude

Knowledge and attitude are critical behavioral determinants of antibiotic adherence and clinical outcomes [33, 34]. Theoretical models such as the Knowledge, Attitudes, and Practice (KAP) model and the Theory of Planned Behavior (TPB) suggest that improved knowledge and positive attitudes toward antibiotic use influence adherence behaviors, which in turn reduce clinical risks such as UTI recurrence [33, 35].

Patient knowledge of antibiotic use, antibiotic resistance, and the importance of completing the treatment will be assessed using a 10-item questionnaire. The item was developed based on the previously reported studies [36–38]. The response will be collected as “true” and “false.” The true response will be scored 1 point and the incorrect response as 0. Attitude toward antibiotic use and adherence will be measured using a 5-item Likert scale, developed based on the previous studies [38–40], with responses ranging from 1 (strongly disagree) to 5 (strongly agree).

The content validity of the tools was established through expert review by two academicians having similar academic backgrounds, one pharmacist and one infectious disease specialist. Discrepancies in item wording were resolved by consensus. A pilot study was conducted with 60 patients. Preliminary reliability demonstrated acceptable internal consistency: Cronbach’s alpha for knowledge = 0.71, and for attitude = 0.73, showing valid internal consistency. Content Validity Index (CVI) analysis showed a scale-level CVI of 0.75 for knowledge and 0.83 for attitude, indicating acceptable validity.

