#### Baseline data

At the start of the study, baseline demographic and patient data will be collected. Additionally, questionnaires regarding knowledge and attitudes will also be collected from all participants. During this stage, patients will be screened based on their prescription filling. Those who filled the prescription will be included for follow-up, while those who did not fill the prescription will be excluded, and the reasons for not filling the prescription will be identified. Data collectors will be trained for intervention implementation and data collection.

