#### Intention-to-treat (ITT) and per-protocol (PP) analysis

##### ITT analysis

The primary analysis will follow the intention-to-treat (ITT) principle and include all randomized participants. We will handle participants with lost to follow-up, missing outcomes, and covariate data using multiple imputations by chained equations (MICE) under a missing-at-random (MAR) assumption [42, 43]. The imputation model will include the primary outcome, baseline covariates predictive of outcome and missingness (age, sex, MPI category, baseline knowledge, and attitude scores). We will generate at least m = max (20, % missing × 1) imputations, fit the planned analysis model within each imputed dataset, and combine estimates using Rubin’s rules [44]. The participants who formally withdraw consent will be excluded from the analysis.

To assess robustness to departures from MAR, we will conduct sensitivity analyses: (1) a complete-case analysis; (2) pattern-mixture/delta-adjustment sensitivity analyses that impose plausible shifts (delta) to imputed outcomes under missing-not-at-random (MNAR) scenarios; and (3) a conservative worst-case/best-case bounds analysis for the primary binary outcome. Results from sensitivity analyses will be reported alongside the primary multiple imputation results and used to assess the robustness of conclusions regarding treatment effect.

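### The covariate list for the adherence model is left open and does not name baseline knowledge and attitude, which the plan collects on everyone and itself treats as predictive of adherence

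*Protocol article*

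**What the plan says.** Under Primary outcome analysis, the protocol article plans two analyses of adherence (yes/no). The first is unadjusted: "The chi-square test or Fisher’s exact test (if expected counts are < 5) will be used for between-group differences". The second is a mixed-effects logistic model, "adjusted for baseline characteristics (e.g., age, sex, MPI category, education", with a hospital term: "Hospital will be included as a random intercept to account for clustering due to stratified block randomization by site". The section does not say which of the two is primary.

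Three other sections bear on the covariates:

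- Baseline data: "questionnaires regarding knowledge and attitudes will also be collected from all participants".
- Knowledge and attitude, under Secondary outcomes: "Knowledge and attitude are critical behavioral determinants of antibiotic adherence and clinical outcomes".
- ITT analysis: the imputation model contains the outcome and "baseline covariates predictive of outcome and missingness (age, sex, MPI category, baseline knowledge, and attitude scores".

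The sample size rests on pilot adherence of "64.3% in the intervention group vs. 48.3% in the control group", and "we used this observed effect size (Cohen’s *h* = 0.32) for power calculation". That is a comparison of two unadjusted proportions.

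**The concern.** Adherence to the current course has no baseline value, so the measured variables closest to it are the knowledge and attitude scores. The protocol treats them as prognostic in two places, but the adherence model offers demographic and socioeconomic variables as its examples and leaves the rest of the list unsettled.

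Two things are at stake. The first is power: a logistic model that conditions on a prognostic baseline variable usually tests the arm effect with more power than one that does not. The second is prespecification: an open list allows the adjustment set to be settled after outcomes are seen. Neutral group labels for the analyst hide which arm is which, but not how far apart the two groups are.

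The covariate lists for the two models of the same outcome also differ in both directions. The imputation list names the scores but not education; the adherence list names education but not the scores.

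**Working it through.** **Inputs from the protocol.** Adherence 64.3% vs 48.3%, two-sided 5% level, 80% power, 152 per group before attrition, 15% attrition, 179 per group enrolled (Patients' population and sample size).

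**The plan's own figure.** h = 2·asin(√0.643) − 2·asin(√0.483) = 0.324. With n = 2(1.960 + 0.842)²/h², the exact h gives 149.5, so 150 per group; the rounded h = 0.32 gives 153.3, so 154. The stated 152 lies between them. For attrition, 152/0.85 = 178.8, so 179. The stated sample size reproduces, and no covariate enters it.

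**Effect of adding a score.** The documents give no correlation between the baseline scores and adherence, so its strength is varied as an assumption. The set-up was:

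- 6,000 simulated trials per row, 152 per arm.
- Marginal adherence held at 64.3% and 48.3%.
- One standard normal baseline score acting linearly on the logit; it stands for the two scores combined.
- Wald test of arm at 1.96, without and with the score.
- No hospital effect and no other covariates.

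Here r is the correlation of the score with adherence. The last column is the squared ratio of mean z statistics, adjusted over unadjusted.

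| OR per SD | r | Power without | Power with | Change (points) | Mean log OR | Mean SE | Effective n |
|---|---|---|---|---|---|---|---|
| 1.00 | 0.00 | 81.0% | 80.8% | −0.2 | 0.663 → 0.665 | 0.2355 → 0.2363 | ×1.000 |
| 1.22 | 0.10 | 79.7% | 79.9% | +0.2 | 0.657 → 0.666 | 0.2354 → 0.2375 | ×1.008 |
| 1.49 | 0.19 | 80.7% | 81.9% | +1.2 | 0.663 → 0.690 | 0.2355 → 0.2412 | ×1.033 |
| 1.82 | 0.27 | 80.4% | 83.5% | +3.1 | 0.659 → 0.717 | 0.2354 → 0.2467 | ×1.075 |
| 2.23 | 0.34 | 80.2% | 84.5% | +4.4 | 0.659 → 0.756 | 0.2354 → 0.2539 | ×1.127 |
| 2.72 | 0.40 | 80.5% | 87.3% | +6.7 | 0.660 → 0.800 | 0.2354 → 0.2621 | ×1.183 |

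Changes are taken before rounding. The simulation error of a single power figure is about √(0.8 × 0.2/6000) = 0.5 points, so the first two rows show no effect.

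**Cross-check.** The usual approximation for effective sample size, 1/(1 − r²), gives 1/(1 − 0.267²) = 1.077 and 1/(1 − 0.400²) = 1.190, against 1.075 and 1.183 simulated.

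**Where the gain comes from.** The standard error of the log odds ratio rises in every row. Power improves because the conditional log odds ratio moves away from zero by more. At r about 0.40 the mean log odds ratio goes from 0.660 to 0.800, which is an odds ratio of exp(0.660) = 1.93 becoming exp(0.800) = 2.23. At r about 0.19 it goes from exp(0.663) = 1.94 to exp(0.690) = 1.99.

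**The case against.** The strongest reply is that nothing has been excluded. The covariates are given as examples, and a journal article may leave the final list to a fuller document. This stands in part: the omission is not a settled exclusion. But the article chose to illustrate the list, its illustration passes over the variables it calls critical, and it gives a definite list for the imputation model.

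Second, an imputation model may properly contain auxiliary variables that the analysis model lacks. This stands, so the scores' presence in one list and absence from the other is not in itself an error. The reverse case is different: education is named for the analysis but not for the imputation.

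Third, if the chi-square test is primary, no covariate list affects it. This stands, because the section does not choose. The ITT analysis section leans towards the model, since it combines model estimates across imputed datasets by Rubin's rules and refers to multiple imputation as primary. That is an inference.

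Fourth, the size of the gain is assumed. This also stands. The statement that knowledge and attitude are determinants is a theoretical rationale and does not quantify how well a 10-item and a 5-item baseline score predict pill counts. Education and poverty category may already carry part of the same information.

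A reader might also infer that the complete-case sensitivity analysis is biased if its model omits variables said to predict missingness. The documents do not support that. Randomization makes the scores independent of arm. If the probability of returning the pack is an arm term times a score term, the scores stay balanced among completers, even when return rates differ by arm. Imbalance needs the relation between score and missingness to differ by arm, and nothing in the protocol says that it does.

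**Conclusion.** The point holds as a badly fixed covariate list that leaves a nearly free improvement unclaimed. The benefit of naming the two scores is a possible gain in power: roughly 0 to +1 point for r up to about 0.2, +3 to +4 points for r about 0.3, and about +7 points for r about 0.4. This rests on an assumed r, on a single score acting linearly on the logit, and on no overlap with the other covariates; overlap would shrink it. If the scores are unrelated to adherence, the loss is negligible (−0.2 points, within simulation error).

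Two stronger readings are tempting and do not hold. One is that the trial gives up precision: in the logistic model the standard error of the log odds ratio rises with adjustment, so its interval would not narrow. The other is that the trial falls short of its stated 80% power: that figure belongs to the unadjusted comparison, reproduces from the stated inputs, and does not depend on adjustment.

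**What to change.** 1. Under Primary outcome analysis, replace the open list with a closed one: arm, age, sex, MPI category, education, baseline knowledge score and baseline attitude score (both scores continuous), with the hospital random intercept.
2. State that this adjusted model, fitted in the imputed datasets, is the primary analysis and that the chi-square or Fisher test is supportive.
3. Under ITT analysis, require the imputation model to contain every covariate of the analysis model. Education is the one now missing from its list; hospital is not named there either and can be settled in the same sentence.
4. State in the report that the odds ratio is conditional on the covariates and so lies somewhat further from 1 than the marginal odds ratio.

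The cost is a few sentences and two degrees of freedom with about 304 analysed participants. No new data are needed. The change should be made before outcomes are compared between the groups, even under neutral labels.

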#### Secondary outcomes analysis

The knowledge and attitude scores will be summed for each participant. Descriptive statistics (mean, standard deviation) will be calculated for both groups, and the mean score will be compared using either independent samples *t*-tests (for normal distribution) or Mann-Whitney *U* tests (for non-normal distribution) for between-group comparison.

UTI recurrence will be a binary variable (yes/no). The chi-square test or Fisher’s exact test (if expected counts are < 5) will be used to compare the proportion of UTI recurrence between the intervention and control groups. Recurrence (yes/no) will be compared between groups using a mixed-effects logistic regression with hospital as a random intercept, adjusted for baseline characteristics. Results will be reported as aORs with 95% CIs.

When multiple comparisons are performed, the Bonferroni correction will be applied to control for the family-wise error rate, ensuring the results remain statistically robust.

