### Randomization

The participants will be randomly assigned to either the VISTA intervention or control (standard care) groups within each hospital using block randomization. Based on the number of hospitals, a unique randomization list will be generated for each hospital. The block size will be six to ensure balanced allocation within each hospital. The block randomization will be conducted through R using the “blockrand” package. An independent researcher, who has no role in participant recruitment or intervention delivery, will generate the list.

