#### Follow-up data

At the follow-up stage, pill counts will measure adherence, and structured questionnaires will be administered to assess changes in knowledge and attitudes regarding antibiotic use. Then, the next follow-up will be done after 1 month, 3 months, and 6 months. At each follow-up, either at the hospital or home visit, the pill count will be performed by the trained data collectors. Returned blister packs will be checked against prescription records. Any discrepancies between the baseline dispensed quantity and the physical count will be documented in site monitoring logs and reviewed by the site supervisor. If packaging is not returned, adherence via pill count will be coded “not verifiable” and treated as missing for the primary pill-count outcome. The details are given in Fig. 8. The overall schedule of enrollment, interventions, and assessments is illustrated in Fig. 9.

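### Knowledge and attitude scores are compared by an unadjusted t-test or Mann-Whitney test with no time point named and no term for baseline score or hospital: valid, but inefficient and loosely defined

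*Protocol article*

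**What the plan says.** The Protocol article names the analysis in Secondary outcomes analysis. "The knowledge and attitude scores will be summed for each participant", means and standard deviations are given by group, "and the mean score will be compared using either independent samples" t-tests when the distribution is normal or Mann-Whitney U tests when it is not. No covariate, hospital term, time point or change score is mentioned.

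The relevant data are collected twice. Under Baseline data, "questionnaires regarding knowledge and attitudes will also be collected from all participants". Under Follow-up data, "structured questionnaires will be administered to assess changes in knowledge and attitudes regarding antibiotic use".

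Elsewhere the article does use hospital and baseline information:
- Randomization: "a unique randomization list will be generated for each hospital".
- Primary outcome analysis: the adherence model is adjusted for baseline characteristics, and "Hospital will be included as a random intercept to account for clustering due to stratified block randomization by site".
- Secondary outcomes analysis: besides a chi-square or Fisher test, recurrence is compared "using a mixed-effects logistic regression with hospital as a random intercept, adjusted for baseline characteristics".
- ITT analysis: the imputation model includes "age, sex, MPI category, baseline knowledge, and attitude scores".

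**The concern.** Adherence and recurrence each get a simple test and also a model with hospital and baseline terms. Knowledge and attitude get only the simple test, and no reason is given for the difference. They are the outcomes for which a baseline value of the same measure exists, and the imputation model already treats that value as predictive.

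Three things follow. Precision that the trial has already paid for is left unused. The compared quantity is not pinned down, because the follow-up section speaks of changes while the analysis section speaks only of a mean score. And the choice between the two tests depends on how the observed scores are distributed, so the data decide whether a difference in means or a rank contrast is tested. The sentence describes both as comparing mean scores, which a Mann-Whitney test does not do.

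At stake are the power and clarity of two secondary comparisons. The primary outcome and the sample size are not affected.

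**Working it through.** **The plan's own figure.** The only sample size stated is for adherence (64.3% against 48.3%, 80% power, two-sided 5%): 152 per group, 179 after 15% attrition. With n = 2(1.960 + 0.842)² / h², the exact h = 0.324 gives 150 and the rounded h = 0.32 gives 154. Also 152 / 0.85 = 179. The stated figures reproduce, and 152 evaluable per arm is used below.

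**Assumed inputs.** The article gives neither the correlation r between baseline and follow-up score nor the intraclass correlation (ICC) by hospital. Ranges are used for both.

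**Baseline adjustment, reading the score as a follow-up score.** The unadjusted test has 80% power at a standardised difference of (1.960 + 0.842) × √(2/152) = 0.321. Adjustment multiplies the residual variance by 1 − r².

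| r | variance factor 1 − r² | equivalent gain in patients, 1/(1 − r²) − 1 | power at 0.321 | detectable difference at 80% | adjusted n per arm matching 152 |
|---|---|---|---|---|---|
| 0.3 | 0.91 | 10% | 83.6% | 0.307 | 139 |
| 0.5 | 0.75 | 33% | 89.9% | 0.278 | 114 |
| 0.7 | 0.51 | 96% | 97.5% | 0.229 | 78 |

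**How far up the range r can go.** The article reports Cronbach's alpha of 0.71 (knowledge) and 0.73 (attitude). If these are taken as the reliability at both visits, the observed r cannot exceed about 0.71 to 0.73. An observed r of 0.7 would need a true-score correlation of 0.7/0.71 = 0.99 or 0.7/0.73 = 0.96. The last row is therefore close to a ceiling, and the first two are the safer guide.

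**If a change score was meant.** With equal variance at both visits, a change score has variance 2(1 − r) times that of a single score: 1.4, 1.0 and 0.6 for r = 0.3, 0.5 and 0.7. The adjusted analysis has 0.91, 0.75 and 0.51, so it is the more precise under this reading too.

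**Chance imbalance at baseline.** The standard error of the baseline difference is √(2/152) = 0.115 SD, so the probability of an imbalance above 0.2 SD is about 8%. An imbalance of 0.2 SD moves the expected unadjusted follow-up difference by 0.2r, which is 0.06, 0.10 and 0.14 SD for the three values of r.

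**Hospital.** Allocation stratified by hospital leaves only the within-hospital variance, a fraction 1 − ICC, in the contrast between arms, while the two-sample test uses the total variance. Its effective critical value is 1.960/√(1 − ICC).

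| ICC | true two-sided alpha | power at 0.321 without hospital | with hospital |
|---|---|---|---|
| 0.01 | 0.049 | 80.1% | 80.4% |
| 0.05 | 0.044 | 80.6% | 82.0% |
| 0.10 | 0.039 | 81.3% | 84.0% |

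The baseline omission matters more than the hospital omission.

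**The case against.** The strongest defence is that the planned test is not wrong. Under randomisation the expected difference between arms in follow-up score equals the expected difference in change, so the t-test and the adjusted model target the same mean difference. Type I error is not inflated, and the variability from chance imbalance is already in the unadjusted standard error. All of this stands.

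A reader might infer several stronger criticisms that the article does not support:
- That the baseline value is certainly discarded. The analysis section does not say which score is compared. A change score, which uses the baseline value, is not excluded, and the baseline scores are kept in the imputation model.
- That an unadjusted comparison cannot address change. For the reason above, the loss is in precision and not in the target.
- That a baseline difference passes whole into the estimate. For a follow-up score, only a fraction r of it does.
- That the cost is near a doubling of the sample. That needs r = 0.7, which the stated reliabilities make barely attainable.
- That repeated measurements are being ignored. The readable text places the questionnaires at the first follow-up. The schedule figures are not legible here, so repetition at 1, 3 and 6 months cannot be assumed.

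It can also be said that a rank test is a common choice for short summed scales, and that the article names no formal normality pre-test. That is fair. The rule still leaves the contrast to be settled by the observed distribution. With about 150 per arm and bounded sums (ten true/false items, five items scored 1 to 5), a comparison of means does not need it.

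The defence that a separate analysis plan may supply the detail is weaker, because the article names the test itself.

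**Conclusion.** The point holds as one of efficiency and definition, not validity. The article sets an unadjusted two-sample test for knowledge and attitude, leaves the compared score undefined, and omits the baseline and hospital terms that it uses for the other outcomes. Reading the score as a follow-up score and assuming r of 0.3 to 0.5, adjustment would cut variance by 9% to 25%, equal to about 10% to 33% more patients. The 49% reduction at r = 0.7 is a near-ceiling. The hospital omission makes the test mildly conservative (alpha 0.049 to 0.039 for an assumed ICC of 0.01 to 0.10) and would not justify a change on its own. The test-selection rule is a smaller, separate fault. The change is worth making, but the trial's main conclusion does not depend on it.

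**What to change.** In Secondary outcomes analysis:
- State that the outcome is the knowledge or attitude score at the first follow-up, at the end of antibiotic treatment, or name another time point if that is intended.
- Replace the choice between t-test and Mann-Whitney with a linear model of each follow-up score on arm, baseline score and hospital. Hospital can be a random intercept, as in the other two models.
- Report the adjusted mean difference with its 95% confidence interval.
- Keep Mann-Whitney as a sensitivity analysis at most.
- Use a repeated-measures model only if the assessment schedule does repeat the questionnaires at later visits.

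The cost is a change of wording, with no new data and no effect on the sample size. It should be dated before group labels are revealed to the analyst. If the sponsor regards it as an important amendment, the article's own rule applies: ethics committee review, an update of the registration, and notice to investigators and sites.

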**Methods:**

In this parallel, two-arm superiority randomized controlled trial, participants with physician-confirmed uncomplicated UTI who have filled an oral antibiotic prescription will be recruited from six tertiary care hospitals in Khyber Pakhtunkhwa, Pakistan. The participants will be randomized in a 1:1 manner to receive either the VISTA intervention or standard care. The VISTA intervention was developed based on nudge theory, guided by the Taxonomy of Choice Architecture framework, and complemented by the MINDSPACE (messenger, incentives, norms, defaults, salience, priming, affect, commitments, and ego) framework. It was developed and validated through a Delphi method, assessing expert feedback, and refined based on a patient understanding study. The intervention sticker uses contrasting colors—red (non-adherence: bacteria evolving into “superbugs”) and green (adherence: antibiotics fully eradicating bacteria)—to communicate the consequences of incomplete versus complete adherence. The primary outcome is adherence, measured by pill count at the initial follow-up. Secondary outcomes include UTI recurrence, knowledge, and attitudes regarding antibiotic adherence. Analysis will follow both intention-to-treat and per-protocol principles.

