### Study design

The study will employ a parallel two-arm superiority RCT design to test whether the VISTA intervention results in higher antibiotic adherence than standard care. Participants will be randomly allocated in a 1:1 ratio to either the intervention group or the control group. For the control group, participants will receive routine care, typically verbal or written instructions about antibiotic use, because it reflects the real-world standard practice for UTI treatment in Pakistan, whereas the intervention group will include VISTA stickers on the antibiotic boxes to improve antibiotic adherence. Both groups will be monitored for their adherence to the prescribed antibiotic course. The details can be seen in Fig. 1.

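### Holm's step-down procedure could replace Bonferroni for the secondary outcomes: same family-wise error control, with more power when more than one effect is real

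*Protocol article*

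**What the plan says.** The multiplicity rule is one sentence at the end of Secondary outcomes analysis in the Protocol article. It says that, where several comparisons are made, "the Bonferroni correction will be applied to control for the family-wise error rate". It states no family and no number of tests.

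The abstract lists the candidates: "Secondary outcomes include UTI recurrence, knowledge, and attitudes regarding antibiotic adherence". Further visits are planned: "Then, the next follow-up will be done after 1 month, 3 months, and 6 months" (Follow-up data). The article does not say whether each visit counts as a comparison.

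The sample size section covers the primary outcome only: "with 80% power at a 5% significance level (two-sided test), 152 participants per group (304 total) would be required". No power or effect size is given for any secondary outcome.

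**The concern.** The only aim given for the correction is control of the family-wise error rate. For that aim Bonferroni is dominated: Holm's procedure keeps the same error bound, needs no assumption about how the tests are related, and never rejects fewer hypotheses. A plan that names Bonferroni therefore gives up some power without tighter control at the chosen level.

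Recurrence is the clinical secondary outcome, and knowledge and attitude are the proposed mechanism. The Knowledge and attitude section expects them to move together: better knowledge and attitudes should improve adherence, which should reduce recurrence. Several real effects at once is the situation in which Holm helps. At stake is the chance of confirming the second and third of these effects once the first has been shown.

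**Working it through.** **1. The plan's own figure.** Inputs from the sample size section: "64.3% in the intervention group vs. 48.3% in the control group", two-sided 5%, 80% power, 15% attrition. Allocation is 1:1 (Study design).

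- h = 2·arcsin√0.643 − 2·arcsin√0.483 = 0.3241, which the article rounds to 0.32.
- n per group = 2·[(1.960 + 0.842)/h]². This gives 149.5, so 150, with h = 0.3241, and 153.3, so 154, with h = 0.32. The stated 152 lies between them.
- 152/0.85 = 178.8, so 179 per group, as stated.

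The figure reproduces with the full 5% spent on the primary outcome. Nothing below changes it.

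**2. Assumptions for the secondary outcomes.** The article gives none of these:

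- The family is m = 3 (recurrence, knowledge, attitude).
- Each true effect has 80% power at unadjusted two-sided 0.05, so its test statistic has mean 1.960 + 0.842 = 2.802.
- The correlation between test statistics is 0, 0.3 or 0.5.

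**3. Bonferroni.** Each p value is compared with 0.05/3 = 0.0167, for which the critical value is 2.394. Power per real effect = Φ(2.802 − 2.394) = Φ(0.408) = 0.658. This depends neither on the correlation nor on how many effects are real.

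**4. Holm.** Order the p values and compare the smallest with 0.05/3 = 0.0167, the next with 0.05/2 = 0.025 and the largest with 0.05/1 = 0.05, stopping at the first failure. The first threshold is Bonferroni's and the later ones are larger. So Holm rejects whatever Bonferroni rejects, and the chance of at least one rejection is the same.

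**5. Size of the difference.** Simulation with 300,000 replicates per scenario; ranges are over correlations 0 to 0.5.

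| Real effects (of 3) | Average power per real effect: Bonferroni | Holm | Power to show all real effects: Bonferroni | Holm |
|---|---|---|---|---|
| 1 | 66% | 66% | 66% | 66% |
| 2 | 66% | 69-70% | 43-51% | 51-57% |
| 3 | 66% | 74-75% | 29-42% | 50-59% |

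With three real effects, the chance of showing at least one is the same under both procedures (87-96%).

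**6. Error control.** With no real effect, the family-wise error rate is identical (0.044 to 0.049). With two real effects and one null it is 0.0161-0.0167 for Bonferroni and 0.0345-0.0365 for Holm. With one real effect and two nulls it is 0.0316-0.0333 and 0.0405-0.0439. Both stay within 0.05. Holm uses part of the allowance that Bonferroni leaves unspent.

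**7. A larger family.** If nine tests counted (for example three outcomes at three visits; correlation 0.3), average power per real effect would be 51% with Bonferroni and 62% with Holm if all nine effects were real. If only three of the nine were real, it would be 51% and 53%. The pattern is the same: the gain grows with the share of effects that are real.

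**The case against.** **Bonferroni is not a mistake.** It is a prespecified, conservative method that delivers the error control the article asks for. No stated figure is wrong, and no section contradicts another on this point. That stands, and it limits the point to an efficiency suggestion.

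**The gain is conditional.** The rule is worded conditionally, the number of tests is not given, and 80% power per secondary outcome is an illustration. A reader might infer that a true effect on any secondary outcome is more likely to be missed. The calculation does not support that: if only one effect is real, the two procedures perform alike (66% and 66%).

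**The primary outcome.** A reader might also infer that the loose wording puts the primary test or the poverty-index subgroups in the same family and so erodes the stated 80% power. The article does not support this. The primary is sized at an unadjusted two-sided 5%. The Bonferroni sentence sits under the secondary outcomes, while the primary test and the subgroups have their own section. Listing the members of the family is also a detail that an article commonly leaves to the full analysis plan, so its absence is not held against the plan here.

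**Confidence intervals.** Bonferroni has simple matching simultaneous intervals and Holm does not. This carries little weight, because the article plans ordinary 95% intervals for recurrence. Intervals matched to three tests would be 100% × (1 − 0.05/3) = 98.3%. No interval that the article promises is lost.

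**Cost.** Recruitment began on August 06, 2025 (Trial status), and the Ethical approval section sends important changes to analyses through the ethics committees, the registry and the sites. The change is therefore small but not entirely free.

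**Conclusion.** The point holds as an optional improvement. Holm's procedure serves the plan's stated aim at least as well as Bonferroni in every case, and better when more than one secondary effect is real. Under the assumptions of three outcomes and 80% unadjusted power each, the gain in average power per real effect is about 0 points with one real effect, 3-4 points with two and 8-9 points with three. The chance of at least one rejection is unchanged. The true size cannot be fixed from the article, because it gives neither the number of tests nor the secondary effect sizes. Bonferroni remains valid, and the power for the primary outcome is not in question.

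**What to change.** Replace the Bonferroni sentence under Secondary outcomes analysis with text to this effect:

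> The primary outcome is tested alone at two-sided 5%. Recurrence, knowledge and attitude form one family, tested by Holm's step-down procedure at a family-wise two-sided 5%, with one prespecified test for each. Results by poverty-index subgroup are outside this family.

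The first clause only writes down what the sample size already assumes.

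One test each has to be named for Holm to be applied. The article currently gives recurrence both a chi-square or Fisher test and a mixed-effects logistic model, and lets the score distribution decide between a t-test and a Mann-Whitney test for knowledge and attitude. Name the time point of each test as well.

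The sample size stays at 152 per group, or 179 with attrition, and no extra data are needed. The cost is a minor amendment to the analysis text, made before any outcome is compared by group.
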